## 2. Materials and Methods

### 2.1. Study Design

The ELECTRO-PAD study is a prospective, randomized, multicenter, single-blind (investigator-blinded), superiority clinical trial with two parallel groups and a primary endpoint of MWD change at 12 weeks following an NMES program. Recruitment for the study commenced in September 2019 and the study end is planned for November 2022.

The study protocol is reported here in accordance with the SPIRIT 2013 recommendations for reporting standard protocol items for Clinical Trials [16]. Information required for those recommendations which could not be directly reported in the manuscript are presented in File S1. Figure 1 shows the schedule of pre-screening, enrolment, interventions, and assessments for the ELECTRO-PAD study. The protocol was reviewed and approved by the sponsor and the applicable French institutional ethical committee (CPP: “*Comité de Protection des Personnes*”) with respect to scientific content and compliance with applicable research and human subjects’ regulations, according to the French law and the Declaration of Helsinki (CPP reference 2018/07). The ELECTRO-PAD study was registered on ClinicalTrials.gov (NCT03795103). A Clinical Research Officer mandated by the promoter ensured participant safety and good practices of the clinical study. The coordinating center was certified to conduct such randomized controlled trial.

In parallel to this clinical trial, two ancillary studies were performed. The first ancillary study was performed only in PAD participants included in the Rennes coordinating center due to material availability. The aim of this ancillary study was to assess the skin microvascular function in the included participants both at visits #1 and #2, between 1 and 14 days after the corresponding visit (Figure 1). A second ancillary study was also performed, but on a distinct group of healthy participants with no intervention. The main aim of this second ancillary study was to determine the normal range for most of the different outcome measures that were performed in PAD participants. In that way, procedures performed by this group of healthy participants were almost the same as those performed by the participants with PAD. Inclusion and Exclusion criteria for healthy participants are reported in File S1 (item 2b).

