Inclusion and exclusion criteria for participants with PAD are displayed in Table 1. In addition, criteria for discontinuing allocated interventions are presented in File S1 (Item 11b). Participants provide paper-based written, informed consent before they participate in the study (File S2), which is collected by the assessor at visit #1 (inclusion visit, Figure 1). At visit #1, the order of the treadmill test and 6 min test is first randomized electronically, and the information is given to the assessor of the local center where the participant performs both tests accordingly. Once visit #1 is achieved, following an electronic process (File S1, Item 16a), each participant is randomized into one of the two arms (1:1) of the study: (1) NMES group; or (2) Control group (CONT). Randomization is performed as block randomization with a 1:1 allocation. The randomization is stratified and equilibrated (block for equilibration not provided here to preserve concealment allocation) in the five inclusion centers. Only the biostatistician, the data manager, and the research associate at the coordinating center have access to the allocation sequence to preserve the allocation concealment. In that way, the assessor of the different outcomes in each center is blinded to the participant treatment group allocation. The research associate of the coordinating center receives an email mentioning the participant group allocation. Then the research associate mails a box containing the following to the participant’s home:for both groups of participants: (i) a box containing the monitors for daily physical activity (PA) and outdoor walking-capacity assessment; (ii) a handbook that explains how to wear the monitors, how to perform the outdoor walking sessions, and that includes a diary to report different information (see below and File S3); (iii) a sealed envelope containing a brochure with advice for regular PA on a day-to-day basis (File S4).for the NMES group only: (i) an opaque box containing the NMES device; (ii) a sealed envelope containing the NMES handbook for implementation and follow-up of the NMES program (Files S5 and S6).

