At the coordinating center, the box is directly hand-delivered to the participant. The research associate calls on each participant once the box is received at their home (identified via a parcel-tracking system). In that way, the research associate indicates the appropriate box to open first and that contains PA monitors. The research associate then explains how to install and wear the monitors verbally while the participants read the guidebook that contains all the information needed. A second call phone is scheduled at the end of the 7-day free-living PA-measurement period during which the research associate discloses the group allocation to the participant.

Due to the nature of the intervention and the follow-up, the participants and the research associate cannot be blinded to allocation, but participants are strongly encouraged not to disclose their allocation status during visit #2. Due to personnel availability at the coordinating center, the assessor of skin microvascular function assessment at both visits (ancillary study #1), and the 6 min walking tests at visit #2 is not blinded to the participant’s treatment arm.

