*6 min walking test.* This test has been widely used in clinical trials in people with PAD to assess walking performance [8,31] and is performed according to standard procedure [31,32]. Among patients with PAD, following supervised and home-based exercise programs (pooled data), a small clinically meaningful change was defined as 12 m and a large clinically meaningful change was defined as 34 m [20]. From the study of the test–retest reliability of the 6 min walking test, Sandberg et al. [33] reported a minimal detectable change of 46 m.

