*Skin microvascular function assessment.* This measure is also performed only on participants included in Rennes due to device availability. Skin microcirculation is measured with the LSCI to assess the modifications of endothelial function at calf and forearm levels [42]. The skin microvascular function is measured after a fasting period. Two different tests are performed: The post-ischemic reactive hyperemia (PORH) and the local thermal hyperemia tests. The PORH test assesses the increase in skin blood flow to tissue that follows the release of a brief 3 min arterial occlusion [43]. The cuff is inflated at a supra-systolic pressure (50 mmHg above the systolic pressure). The PORH test, which is expected to be endothelium dependent and involving both myogenic and metabolic factors, evaluates the reperfusion of the vascular beds and is characterized by a peak in the skin blood flow after the cuff release [42]. Local thermal hyperemia is obtained with a special probe (42 °C–44 °C) that leads to a sustained increase in skin blood flow that is biphasic: an initial peak that is axon-reflex mediated, and a sustained plateau phase that depends on nitric oxide [44]. The LSCI was preferred to the laser Doppler flowmetry due to a better reproducibility [45]. Skin blood flow is expressed in arbitrary units or as multiples of the baseline.

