## 3. Discussion

Lower-extremity electrical stimulation is an older technique that has regained recent interest in the treatment of lower extremity functional impairment of people with PAD, as shown by recently published original and protocol studies [49,50,51,52]. Owing to the very low number of available studies with adequate sample size and low risk of bias, a recent systematic review concluded that no clear clinical indication could be drawn regarding the efficacy of NMES for the management of impaired walking function in patients with PAD [13]. The multicenter, investigator-blinded, randomized controlled ELECTRO-PAD clinical trial will contribute to increase the level of scientifical evidence regarding the efficacy on NMES on walking capacity in people with lower extremity PAD.

One strength of the ELECTRO-PAD clinical trial is the duration of the NMES program. As compared to previous studies that assessed the effect of an NMES program on walking capacity during four-week or a six-week programs [12,14,49], the NMES program of the ELECTRO-PAD trial is longer, with a three-month program duration which duplicates the recommended duration for SET programs [8]. It will be of interest to observe the magnitude of change (if any) in walking capacity from the ELECTRO-PAD trial compared to previous NMES programs and SET programs.

Another strength of the ELECTRO-PAD clinical trial relies on the methods used for the assessment of walking capacity. Compared with previous studies [12,14,49], the ELECTRO-PAD clinical trial will assess the walking capacity of PAD participants through three complementary walking assessment tests: the modified Strandness treadmill test, the six-minute walking test, and a GPS-assessment of outdoor walking capacity. Although this increases the complexity of the protocol, this methodologic choice was deemed important considering the existing controversy about the best functional test for measuring response to interventions in PAD [31,53,54]. It has been shown that walking capacity assessment tests provide outcomes that are not interchangeable in participants with PAD [55]. The ELECTRO-PAD clinical trial will show whether, and how, an NMES program impacts differently walking capacity changes according to the outcome measure that is considered.

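### The blinding statement and the investigator-blinded label need qualifying: at the coordinating centre the follow-up 6 min walk and all skin microvascular tests are assessed unblinded

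*Protocol article*

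**What the plan says.** All references are to the protocol article.

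- **General rule (Section 2.2).** After describing who can see the allocation sequence, the article concludes that "the assessor of the different outcomes in each center is blinded to the participant treatment group allocation". The sentence has no qualifier.
- **Label.** Section 2.1 describes a "prospective, randomized, multicenter, single-blind (investigator-blinded), superiority clinical trial with two parallel groups". Section 3 repeats it: "The multicenter, investigator-blinded, randomized controlled ELECTRO-PAD clinical trial".
- **Exception (later in Section 2.2).** "Due to personnel availability at the coordinating center, the assessor of skin microvascular function assessment at both visits (ancillary study #1" is how the sentence begins; it ends by adding that "the 6 min walking tests at visit #2 is not blinded". I read the whole sentence as applying to the coordinating centre only.
- **Status of the two measures (Section 2.5).** Both are listed secondary outcomes: the 6 min walk is item (ii), skin microvascular function item (xi).
- **Where and when microvascular function is measured.** Section 2.6.2: "This measure is also performed only on participants included in Rennes due to device availability". Section 2.1 places the tests "both at visits #1 and #2, between 1 and 14 days after the corresponding visit".
- **Analysis (Section 2.8).** Changes from baseline in primary and secondary outcomes are compared between arms with a two-sample t-test or Mann–Whitney test. Regression adjustment is foreseen for baseline imbalance and sensitivity analyses for missing data. Neither concerns assessor blinding.
- **Limitations (Section 3).** The unblinded assessments are not mentioned.

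**The concern.** The 6 min walk depends on effort and can respond to the assessor's encouragement. At the coordinating centre the assessor of the follow-up walk is unblinded, and participants know their allocation at every centre. On that test, neither side is masked there.

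This matters for interpretation. Section 3 presents the three walking tests as a strength and intends to show whether the intervention affects walking capacity differently depending on the test. If the treadmill is assessed blinded and the 6 min walk partly unblinded, a difference between their results could reflect assessment conditions. A reader who relies on the general rule or the label would not consider that explanation.

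For microvascular function the label does not describe the data at all, because no part of that outcome is assessed blinded.

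**Working it through.** **1. The plan's own figure.** No stated figure depends on this point. The sample size concerns the primary outcome (Section 2.7: difference 58 m, SD 78 m, two-sided alpha 0.05, power 80%). It reproduces: 2 × (1.960 + 0.842)² × 78² / 58² = 28.4, rounded up to 29 per group. Blinding of the secondary outcomes does not alter it.

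**2. How an assessor effect reaches the 6 min walk result.**
- The visit #1 walk is done before randomisation (Section 2.2), so allocation cannot influence it.
- The visit #2 walk at the coordinating centre is assessed with allocation known.
- The change score is visit #2 minus visit #1, so an arm-dependent effect at visit #2 is not cancelled by the baseline value.
- Randomisation is stratified by centre. This balances the arms within the coordinating centre but does not remove an effect that arises after allocation.

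**3. What would be needed for this to matter (illustration on assumed values).** Let f be the coordinating centre's share of analysed participants and b the shift in the arm difference there caused by unblinded assessment. With 1:1 allocation within centres and a comparison of means, the overall difference shifts by f × b. The article gives neither: Section 2.2 says that centres had no recruitment share to reach, and nothing is said about b.

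| Assumed f | b = 10 m | b = 20 m | b = 30 m | b needed for a 12 m shift (12 / f) |
|---|---|---|---|---|
| 0.2 | 2 m | 4 m | 6 m | 60 m |
| 0.4 | 4 m | 8 m | 12 m | 30 m |
| 0.6 | 6 m | 12 m | 18 m | 20 m |
| 0.8 | 8 m | 16 m | 24 m | 15 m |

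Section 2.6.2 gives three benchmarks for this test: "a small clinically meaningful change was defined as 12 m", a large change of 34 m, and a minimal detectable change of 46 m. No cell reaches 34 m, and only those with a large share and a sizeable effect reach 12 m. The table shows what would have to be true. It does not estimate the bias.

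**4. Microvascular function.** Only the coordinating centre contributes data, so there are no blinded centres to mix with or to compare against. Randomisation follows visit #1, and the baseline test is done 1 to 14 days after that visit. The baseline value can therefore also be recorded by someone who knows the allocation, which fits the statement that the assessor is unblinded at both visits.

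**5. Price of leaving out the coordinating centre.** With equal variances, the standard error grows by 1/√(1 − f). Of 80 randomised, before dropout:

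| Assumed f | Remaining: 80 × (1 − f) | Standard error multiplied by |
|---|---|---|
| 0.2 | 64 | 1.12 |
| 0.4 | 48 | 1.29 |
| 0.6 | 32 | 1.58 |
| 0.8 | 16 | 2.24 |

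The remaining centres are still a randomised comparison because of the stratification, but a small one if the coordinating centre recruits heavily.

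**The case against.** The strongest reply is that the article hides nothing. The exception stands in the same section as the general rule and names the outcome, visit, centre and reason. That is right: this is a wording conflict to reconcile, and a reader who infers concealment goes too far.

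A reader might also infer that the results are to be pooled as though they were blinded. The article does not say so. For the 6 min walk it describes one comparison and no separate handling, which means mixing. Section 2.8 refers to File S1, item 20a, which was not available, and an analysis by centre could be specified there or in an analysis plan. For microvascular function the pooling argument fails outright, since there is only one centre.

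Three further points stand:

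- The 6 min walk is said to follow a standard procedure, which may limit assessor influence. It does not make an unblinded assessor blind.
- Laser speckle imaging is recorded by an instrument, which leaves less room for judgement than a walking test. Acquisition and reading still involve an operator, and the article does not say whether recordings are masked.
- The other centres are not free of bias, because participants know their allocation everywhere. An estimate without the coordinating centre would also carry every other difference between centres. It should therefore not replace the overall result.

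What the reply does not answer is the unqualified rule and label, the absence of the exception from the limitations, and the planned comparison between walking tests.

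**Conclusion.** The point holds as a needed qualification and an inexpensive safeguard for two secondary outcomes. The 6 min walk is partly unblinded at follow-up. Microvascular function is assessed unblinded throughout, possibly including its baseline. The general rule in Section 2.2 and the label in Sections 2.1 and 3 do not reflect this.

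The size of any bias in the 6 min walk is unknown. It is the product of two quantities that the article does not give, and the values tabulated are assumptions. It would be minor if the coordinating centre's share is small and could matter if that share is large.

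A reader might infer that the primary result is compromised. The documents do not support that: the exception does not name treadmill maximal walking distance, and the sample size is unaffected. Nor do they show that a positive 6 min walk result would be spurious.

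**What to change.** 1. **Wording.** In Section 2.2, limit the general rule to the outcomes and centres where it applies. Qualify the investigator-blinded label in the same way in Sections 2.1 and 3, and list the unblinded assessments among the limitations.
2. **6 min walk.** If not already planned, pre-specify a sensitivity analysis without the coordinating centre, or an analysis by centre, and report it beside the overall result. The overall analysis remains the governing one. If the two estimates diverge, caution against reading a difference between the 6 min walk and the treadmill as a treatment effect.
3. **Microvascular function.** Code the laser speckle recordings for arm and visit before off-line reading, and report the outcome as acquired unblinded. Coding masks the reading, not the acquisition.

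No extra assessor, visit or participant is needed. The costs are one additional analysis, whose estimate is less precise than the overall one, and some data-management time to code the files.

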### 2.3. NMES Intervention

Participants allocated in the NMES group are equipped with a VEINOPLUS^®^ device (Ad Rem Technology, Paris, France). The device consists of a handheld central unit that works on a battery, connected to two ovoid skin-adhesive electrodes (Figure 2). Each electrode is ~5 cm wide and 10 cm long. For the participants with mainly unilateral symptoms limiting walking performance, the two electrodes are positioned on the symptomatic and limiting calf (Figure 2). The stimulation consists of a series of rectangular pulses of low energy (<25 mC), low voltage (50 Vpeak), and low frequency (1–250 Hz), with maximum duration of impulse of 240 ms. Intensity can be set manually. The shape of the current wave is biphasic, leading to nearly symmetric contractions of the heads of the calf muscle. For the participants with bilateral calf symptoms, two electrodes are positioned first on their right or left calf during half of the program session, then on the other calf for the other half of the session. Participants are asked to adopt a sitting or semi-extended position for better stimulation efficiency. The participant can perform other intellectual activities during the session but should avoid movements and displacements. The intensity of stimulation is regulated by the participants themselves because there is interindividual variability in the felt effect of electrical stimulation [15]. The intensity is indicated on the screen of the device by a number corresponding to the level of intensity reached (Figure 2). The participants are asked to select gradually the highest possible stimulation intensity until he/she sees and feels deep contractions of the calf without pain.

The NMES program is performed at home and is delivered 5 days a week across the program (i.e., 12 weeks) with 2 h/day of NMES on weeks 3 to 6 and weeks 9 to 12, and 3 h/day on weeks 1, 2, 7, and 8. Each NMES session lasts a minimum of 1 h and a maximum of 2 h. The time of the day to complete the sessions is left free to the participants (Files S5 and S6).

To enhance validity of data, for each NMES session, participants are asked to report the following information in a diary: stimulated calf(s), NMES intensity level maintained during the session, cumulated total duration reached at the end of the session, and feelings about the session. To assess protocol adherence, the ratio of the total duration of NMES reached at the end of the protocol over the expected total duration will be used in future analyses. In addition, phone calls are also conducted every two weeks (±4 days) to record information about the NMES program to ensure the correct functioning of the device, check the correct number of hours of NMES performed, promote participant retention, and complete follow-up. The participants are also asked to indicate whether any changes in symptoms, comorbidities or walking activity potentially occurred. Furthermore, participants in the NMES group receive a brochure with advice for engaging in daily PA (File S4).

### 2.4. Non-Intervention Control Group

Participants in the CONT group only receive a brochure with advice for engaging in daily PA. Phone calls are also conducted every two weeks (±4 days) to record any potential symptoms, comorbidities, or walking activity changes, promote participant retention, and complete follow-up.

### 2.5. Primary and Secondary Outcomes

Details are presented in File S1 (Item 2b). The primary outcome of the ELECTRO-PAD study will be the change in MWD at 12 weeks as assessed by a modified Strandness treadmill test (see outcomes assessment).

Secondary outcomes will be changes at 12 weeks in: (i) treadmill pain-free walking distance (PFWD); (ii) 6 min total walking distance; (iii) global positioning system (GPS)-measured outdoor walking capacity; (iv) ankle-brachial index (ABI); (v) daily PA level, including walking pain-manifestation assessment (see below); (vi) walking impairment questionnaire (WIQ) sub-scales and total scores; (vii) short-form health survey (SF36) score; (viii) peripheral artery questionnaire (PAQ) score; (ix) dietary questionnaire score; (x) delta from resting oxygen pressure (DROP) using TcPO_2_ during treadmill walking test and (xi) skin microvascular function assessed both at the forearm and calf levels using the laser speckle contrast imaging (LSCI) technique; and (xii) maximal walking distance according to the location of the arterial obstruction (using scan images).

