### 2.8. Data Collection, Management, and Analysis

*Data collection and management.* The data collected are in an electronic Case Report Form (eCRF) and data monitoring is carried out on a regular basis (~every six months).

*Statistical analysis (see also File S1, item 20a).* Descriptive statistics will be performed to describe the baseline characteristics of interest at the level of the two groups and for the different outcomes. Continuous data will be expressed as mean +/− standard deviation or median values with interquartile range, depending on the distribution. A normality test will be carried out to judge the Gaussian or non-Gaussian distribution of the data of the continuous variables studied. Two-sample, two-sided t-tests (or Mann–Whitney U test) and χ2 tests will be used to compare continuous and categorical characteristics of participants across the two groups at baseline, respectively.

For statistical analysis of the primary and secondary outcomes after study completion, two -sample, two-sided t-tests (or Mann–Whitney U test if the data is not normally distributed) will be used to compare changes in outcomes between baseline and the 3-month follow-up between the NMES and the CONT groups. However, in case of imbalance in baseline characteristics between the 2 groups, outcome data will be analyzed using linear regression models adjusting for significantly different baseline data between the two groups [46].

Firstly, an intention-to-treat analysis will be performed. As recommended [47], a missing at random (MAR) assumption will be made for missing data for principal analysis by performing complete cases and multiple imputation analysis. Deviation from MAR will also be assessed with sensitivity analysis under the missing not at random (MNAR) assumption, using controlled multiple imputation with different controlled scenarios. A per-protocol analysis will be also performed considering only participants with data available both at visit #1 and visit #2.

A subgroup analysis will be performed to explore the potential association between change in treadmill MWD and reported walking activity changes during the follow-up. In the NMES group, potential association between the total dose of NMES over the program and change in treadmill MWD will be assessed.

Statistical analysis will be carried out using R software [48]. The level of significance will be fixed at *p* < 0.05.

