Finally, the participants with bilateral lesions apply NMES on one calf during half of the program session, then on the other calf for the other half-session. Thus, the duration of the NMES session for each limb for participants with bilateral lesions is two times less than the session duration for participants with a unilateral lesion. The device used does not allow the user to simultaneously connect two pairs of electrodes (i.e., one for each limb). Another possible solution could have been to use two devices simultaneously in participants with bilateral lesions. However, we did not choose this solution because we expected this could have been too burdensome for those participants, increasing the risk of low adherence to the NMES program or dropout. The inclusion of participants with bilateral lesions is deemed important for a wider applicability of NMES intervention in people with PAD in the future. We foresee that there will be few participants with walking limitations due to strictly equal bilateral symptoms at the calf level. Nevertheless, we will assess whether the change in maximal walking distance differs according to the participant’s symptom profile (i.e., bilateral vs unilateral).

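### Secondary outcome (xii) is the primary outcome split by arterial location, and the article's only stated test for secondary outcomes cannot show whether the NMES effect depends on location

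*Protocol article*

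**What the plan says.** Section 2.5 defines the primary outcome: "The primary outcome of the ELECTRO-PAD study will be the change in MWD at 12 weeks". The secondary list then opens with "Secondary outcomes will be changes at 12 weeks in", and its last item, (xii), is "maximal walking distance according to the location of the arterial obstruction (using scan images".

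Section 2.8 gives one analysis rule, introduced by "For statistical analysis of the primary and secondary outcomes after study completion". Two-sided two-sample t-tests, or Mann–Whitney tests if the data are not normal, "will be used to compare changes in outcomes between baseline and the 3-month follow-up between the NMES and the CONT groups". The significance level is p < 0.05. If baseline characteristics are imbalanced, linear regression adjusting for them replaces the simple test.

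Two related questions are worded differently:
- **Section 2.8, walking activity:** "A subgroup analysis will be performed to explore the potential association between change in treadmill MWD and reported walking activity changes during the follow-up".
- **Discussion, bilateral versus unilateral symptoms:** "we will assess whether the change in maximal walking distance differs according to" the symptom profile.

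Section 2.2 stratifies randomization by center and does not mention arterial location. Sections 2.5 and 2.8 refer to File S1 (items 2b and 20a) for further detail.

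**The concern.** Most of the secondary list consists of measurements other than treadmill MWD. Item (xii) is not a new measurement. It is the primary variable broken down by where the arterial obstruction lies, which makes it a subgroup question. Placing it among the secondary outcomes brings it under a rule written for ordinary outcomes.

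That rule compares two arms, which leaves few ways to apply it to (xii). Pooling the locations would only repeat the primary test. A contrast of the arm effect between locations is not a two-sample test. The regression option adjusts for imbalanced covariates and is not described as containing an interaction. What remains is a separate NMES versus control test within each location.

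A set of within-location p-values does not tell the reader whether the effect depends on location. Each location holds a fraction of a trial sized for one overall comparison, so one location can reach p < 0.05 and another miss it when the true effect is the same in both. The pattern could then be read as NMES working at one arterial level and not at another.

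**Working it through.** **Inputs.** Section 2.7 gives a difference of 58 m, SD 78 m, alpha 0.05, power 80%, about 29 per group, and 80 in total (40 per group) with at most about 30% dropout. The test is two-sided (section 2.8). The number and size of location classes are not given. I assume 2 or 3 equal classes.

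**1. The plan's own figure.** n per group = 2 × (1.960 + 0.842)² × (78/58)² = 2 × 7.85 × 1.809 = 28.4, rounded up to 29. The stated 29 reproduces. With 40 per group and 30% loss, 28 per arm remain, so 28 to 40 completers per arm is a reasonable range.

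**2. Power within one location.** Two-sample t-test, standardized effect 58/78 = 0.744.

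**3. Chance of discordant significance when the true effect is 58 m everywhere.** With k independent classes each having power p, the chance that some are significant and some are not is 1 − p^k − (1 − p)^k.

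| Completers per arm | Locations | Per arm in each | Power p | Discordant |
|---|---|---|---|---|
| 28 | 2 | 14 | 0.474 | 1 − 0.474² − 0.526² = 0.50 |
| 28 | 3 | 9 | 0.317 | 1 − 0.317³ − 0.683³ = 0.65 |
| 40 | 2 | 20 | 0.630 | 1 − 0.630² − 0.370² = 0.47 |
| 40 | 3 | 13.3 | 0.454 | 1 − 0.454³ − 0.546³ = 0.74 |

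Full retention does not remove the problem. With three locations it makes discordance more likely.

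**4. Chance findings when NMES has no effect anywhere.**
- At least one location significant in either direction: 1 − 0.95² = 9.8%; 1 − 0.95³ = 14.3%.
- At least one location significant in favour of NMES: 1 − 0.975² = 4.9%; 1 − 0.975³ = 7.3%.
- Overall test not significant but at least one location significantly favouring NMES (simulation, 28 per arm): about 3% for two locations and 6% for three.

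**5. What an interaction test could detect.** For two equal locations with N per arm, the SE of the difference between location-specific effects is 78 × √(4/(N/2)). Power for a 58 m difference is Φ(58/SE − 1.96). The difference detectable with 80% power is 2.80 × SE.
- N = 29: SE = 41.0 m, power 29%, detectable difference about 115 m.
- N = 40: SE = 34.9 m, power 38%, detectable difference about 98 m.

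With a 70:30 split of locations, power falls to 25% and 33%. The detectable differences exceed the planned main effect of 58 m, so the location question can only be exploratory in this trial.

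**The case against.** **The within-location step is inferred.** Section 2.8 never mentions location or a test within a class. This is true. The inference rests on there being no other way to apply a two-arm test to (xii) without repeating the primary analysis. A reader might go further and infer that the plan commits to location-specific significance claims. The article does not support that, since it promises no claim for any location.

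**The authors may intend the right question.** The Discussion words the parallel symptom-profile item as whether the change differs, and (xii) uses a similar phrase. This reading is possible. It shows that the authors can state the effect-modification question, but the article places (xii) in the secondary list under the between-arm rule.

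**File S1 may settle it.** Location categories, an interaction model or an exploratory label could be there. Their absence from a condensed article is not an error, and none is claimed. The point concerns what the article does state: how (xii) is classed and which test applies to that class.

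**The false-positive risk is modest in the direction that matters.** The 10% to 14% figures are two-sided and include locations where NMES looks harmful. In favour of NMES the figures are 5% to 7%. This stands, so the weight falls on false contrasts between locations.

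**Removing a published secondary outcome from a trial already recruiting could look like outcome switching.** This also stands, and the fix therefore relabels (xii). Banning within-location p-values outright would be a reporting preference.

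**Conclusion.** The point holds in a limited form. Item (xii) is a subgroup analysis of the primary outcome, and the only rule the article states for its class cannot answer the question it poses. If that rule is applied within locations and NMES has the same 58 m effect everywhere, the locations would disagree on significance about 47% to 74% of the time. With no effect, at least one location would significantly favour NMES about 5% to 7% of the time.

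These figures assume 2 or 3 equal-sized locations, SD 78 m and 28 to 40 completers per arm. The number and sizes of the locations are assumptions. A reader might infer that the trial's main conclusion is at risk, but the primary comparison and its sample size are untouched. The change is worth making because it is nearly free and gives a better answer than the stated rule.

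**What to change.** Keep (xii) as a pre-declared item, but describe it in section 2.5 as an exploratory effect-modification analysis of the primary outcome. In section 2.8, specify one model for MWD change with arm, location (classified from baseline imaging) and arm-by-location. Report the arm difference with its 95% confidence interval for each location, together with the interaction test. Base any location-specific statement on the interaction, not on which locations reach p < 0.05. If File S1 already says this, the article should state it or point to it for this item.

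The cost is about one sentence in each section, with no new data and no change to trial conduct. The downside is that the analysis becomes openly exploratory, with wide intervals and the low interaction power shown above.
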